# Acupuncture combined with traditional Chinese medicine e-aid cognitive behavioral therapy for insomnia (TCM-eCBT-I) for chronic insomnia: study protocol for a randomized controlled trial

**DOI:** 10.1186/s13063-022-06012-6

**Published:** 2022-01-28

**Keywords:** Acupuncture, e-aid cognitive behavioral therapy for insomnia, Chronic insomnia, PSQI, Randomized controlled trial

## Abstract

**Introduction:**

The incidence of insomnia is getting higher and higher. Long-term insomnia seriously affects people’s health. Drug use is usually accompanied with adverse events. Both acupuncture and cognitive behavioral therapy for insomnia (CBT-I) have been proven to be safe and effective non-pharmacological treatments for insomnia. As the insomniacs’ bad sleep behavior and wrong cognition have not been effectively corrected, acupuncture has a quick effect, high patient compliance but unstable long-term efficacy, while CBT-I is complex, time-consuming, and expensive; additionally, patient compliance is low, and the number of trained therapists is limited, making it difficult to carry out. Therefore, this study aims to use the insomnia TCM system to construct a convenient and feasible traditional Chinese medicine e-aid cognitive behavioral therapy for insomnia (TCM-eCBT-I) for Chinese people, and combine the advantages of acupuncture and TCM-eCBT-I for maintaining long-term efficacy, and three treatments will be evaluated to provide clinicians with a more effective clinical protocol

**Methods and analysis:**

This study is a single-center, open-label, randomized controlled trial. Ninety subjects will be recruited and randomly assigned to three groups: the acupuncture group, the TCM-eCBT-I group, and the acupuncture combined with TCM-eCBT-I group, in a ratio of 1:1:1. We will evaluate the Pittsburgh Sleep Quality Index (PSQI) and Dysfunctional Beliefs and Attitudes About Sleep Scale (DBAS), Insomnia Severity Index (ISI), sleep diary, Hamilton Anxiety Scale (HAMA), Hamilton Depression Scale (HAMD), and Fatigue Scale-14 Scale (FS-14) scales. All adverse reactions will be assessed through the ADVERSE event table. All outcomes will be evaluated online at 0 weeks, 4 weeks, 8 weeks, 16 weeks, and 28weeks.

**Ethics and dissemination:**

This study has been approved by the Institutional Review Board of the Affiliated Hospital of Nanjing University of Chinese Medicine (2020 NL-018-02). Informed consent will be obtained from all the subjects. The results will be shared with sleep researchers, public, and relevant academic institutions through high-impact peer-reviewed publications.

**Trial registration:**

Chinese Clinical Trial Registry ChiCTR2000032960. Registered on 17 May 2020

## Strengths and limitations

A single-center, open-label, randomized controlled trial strictly follows the principles of CONSORT and STRICTA.It is the first time to investigate the long-term efficacy and safety of acupuncture combined with TCM-eCBT-I in treating chronic insomnia.Subjects will be conveniently evaluated online and followed up for a long time through the insomnia TCM system.Recruitment of this study is limited to one center of Chinese first-class hospitals, and the sample size is too small so that the results may not be applicable to other levels of hospitals or other countries.This study cannot blind subjects, which may lead to bias and affect the results.

## Background

With fierce social competition, accelerated pace of life, and the increasing mental stress, the incidence of insomnia is getting higher and higher. About 10 to 20% of people in the world suffer from insomnia, while the prevalence of insomniacs in adult is 33 to 50% [1, 2]. Long-term insomnia affects the neuroendocrine immune network system, resulting in multiple organ dysfunction and decreasing immune function and is often accompanied by anxiety and depression, daytime fatigue, cognitive dysfunction, and other injuries [3–5]. It can even cause traffic accidents, endanger personal and public safety, and place heavy burden on society and families [6–8]. Therefore, it is crucial for both individuals and the public to keep a healthy sleep without insomnia.

At present, there are many treatments for insomnia. Drug therapy is convenient, fast-acting, and still the most common treatment for insomnia [9]. However, a large number of studies have shown that long-term drug use is usually accompanied with adverse events, including ineffectiveness, drug resistance, forgetfulness, nightmare, and cognitive impairment [10]. Most insomniacs are eager to seek effective and safe treatments for insomnia. In the past two decades, non-pharmacological treatments have attracted increasing attention [11].

Acupuncture, as a natural therapy with a long history, has been widely used in Asian countries such as China and South Korea, because of its advantages of safety, effectiveness, and convenience [2]. According to a survey of private clinics, insomnia is one of the top ten acupuncture indications in the USA [12]. In recent years, more and more evidence has shown that acupuncture is safe and effective in treating insomnia [13–19]. Acupuncture is also included in Chinese guidelines for the diagnosis and treatment of insomnia [20]. However, as patients’ bad sleep behavior and wrong sleep cognition are not effectively corrected, the effect of acupuncture is usually short-term. In addition, most clinical studies seldom include long-term follow-up. Thus, the long-term effect of acupuncture on insomnia is still unclear.

Most insomnia diagnosis and treatment guidelines recommend CBT-I as the first choice [20–22]. Some meta-analyses suggest that CBT-I is effective for primary insomnia [23] and comorbidity insomnia [24]. It can improve sleep quality by changing the wrong cognition and behavior factors of insomniacs and can enhance confidence in self-controlled insomnia [25]. Compared with drugs, CBT-I can improve sleep quality for up to 3 years, with minimal risks [23, 26]. Up to now, traditional face-to-face CBT-I usually needs 8 interviews, which is time-consuming, laborious, and expensive. In addition, the number of therapists who have received formal training is limited. In fact, only a few patients can benefit from CBT-I [27]. Both acupuncture and CBT-I have proven to be safe and effective non-pharmacological treatments for insomnia. Most acupuncture studies usually choose positive drugs or placebo as control. Only a few randomized controlled trials directly compare acupuncture and CBT-I in treating insomnia, but the conclusion is still unclear [28]. With the rapid development of the Internet, in order to improve the feasibility of CBT-I and to benefit more patients, eCBT-I through personal intelligent terminals has become a trend in insomnia [29, 30]. Compared with traditional face-to-face CBT-I, it has advantages of convenience, flexibility, low cost, less dependence on doctors, and high patient compliance [31, 32]. Recent studies have shown that the effect of eCBT-I is equivalent to traditional face-to-face CBT-I [33]. English-speaking countries have provided several eCBT-I softwares (such as Sleepio and SHUTI), which show similar efficacy to standard CBT-I. However, there are few CBT-I suitable for Chinese people, and no relevant clinical research data has been found, so further exploration and verification are needed to test its efficacy [34–36].

In the early stage, we developed the insomnia TCM system for chronic insomnia based on WeChat public platform (software copyright, registration number: 2019SR0900086), which is used for TCM diagnosis, information collection, and management of chronic insomnia. It includes modules such as sleep self-test, personal files, tracking, and health education. Baduanjin exercise is a popular traditional Chinese fitness method that combines physical movement, breathing, and psychological adjustment. By stimulating the meridians and organs, [37, 38] it can improve sleep. Five-element music guided by the basic theory of traditional Chinese medicine has a unique curative effect in treating insomnia [39]. We can make a comprehensive analysis according to the syndrome differentiation of patients and choose the corresponding treatment strategy [40, 41].

In order to take advantage of the unique advantages of traditional Chinese medicine in treating insomnia and to explore suitable eCBT-I for Chinese people, this study realizes eCBT-I based on the health education module of the insomnia TCM system, incorporating the Baduanjin exercise and the five-element music, to form TCM-eCBT-I. This study aims to construct a convenient and feasible TCM-eCBT-I, to combine the advantages of acupuncture and TCM-eCBT-I, and to explore the chronic disease management model of acupuncture in the treatment of chronic insomnia. Meanwhile, the short-term and long-term efficacy of acupuncture, TCM-eCBT-I, and acupuncture combined with TCM-eCBT-I will be evaluated to provide information for clinical decision-making. Our hypothesis is that acupuncture combined with TCM-eCBT-I is more effective than TCM-eCBT-I or acupuncture single therapy.

## Methods and design

### Study design

This study is a single-center, open label, randomized controlled trial and will be completed in the insomnia clinic of the Acupuncture and Rehabilitation Department of the Affiliated Hospital of Nanjing University of Chinese Medicine from 01 June 2020 to 30 December 2021. This study follows the principles of Consolidated Standards of Reporting Trials (CONSORT), [42] and Standards for Reporting Interventions in Clinical Trials of Acupuncture(STRICTA) [43] will recruit 90 subjects and randomly assign them to the acupuncture group, the TCM-eCBT-I group, and the acupuncture combined with the TCM-eCBT-I group, at a 1: 1: 1 ratio. Subjects will be interviewed before recruitment, by completing a structured insomnia diagnosis process (refer to the 2017 China Sleep Diagnostic [44] - Insomnia Diagnosis Process) to diagnose chronic insomnia, and they will be screened for other sleep disorders, mental disorders, and serious physical diseases and through formal medical history and sleep symptoms. All subjects also need to take PSQI assessment and record one week sleep diary in order to obtain baseline assessment data. Subsequently, 4 weeks of treatment and 24 weeks of follow-up will be conducted.

All subjects will complete the following scale evaluation: PSQI, ISI, and sleep diary to evaluate sleep; DBAS to evaluate sleep cognition and belief; HAMA and HAMD to evaluate mental state; and FS-14 to evaluate mental and physical fatigue. The above scales will be evaluated online in the insomnia TCM system during the 0th week, 4th week, 8th week, 16th week, and 28th week. Subjects will sign an informed consent form after evaluating the conformity for inclusion. The test process is shown in Fig. 1, and the time point of the assessment is shown in Fig. 2.

**Fig. 1 Fig1:**
[figure not shown]
The test process

**Fig. 2 Fig2:**
[figure not shown]
The time point of the assessment

### Study setting and recruitment

The recruitment will take place in the Affiliated Hospital of Nanjing University of Chinese Medicine, which is a large third-class grade A comprehensive hospital with good performance in clinical medicine and scientific research. Currently, it is an international acupuncture clinical training base of the World Health Organization and an international traditional medicine cooperation center. In this study, we will use the electronic screen recruitment and publicity of hospitals, tweets on insomnia TCM system, two-dimensional code scanning leaflets to fill in the registration form, and telephone registration to recruit subjects. The duration is 29 weeks for each subject, including 1 week of baseline period, 4 weeks of treatment period, and 24 weeks of follow-up.

### Randomization and allocation concealment

The statistical expert from the Faculty of Medical Statistics and Epidemiology from the Affiliated Hospital of Nanjing University of Chinese Medicine will use the statistical software SPSS (IBM SPSS statistics version 22.0, USA) to generate 3 different random number lists, each of which contains 30 numbers. The random numbers in each list will be sorted in ascending order. The randomization schedule calculated in no. 1–30 is the acupuncture group, no. 31–60 is TCM-eCBT-I group, and no. 61–90 is the acupuncture combined with TCM-eCBT-I group. According to the disclosed method, [45] the allocation sequences are enclosed in sealed envelopes with a unique identification number. The envelope will be sent to an investigator in charge of the group assignments. The investigator will specify in the envelope who and when to open the randomly assigned envelope. The number will appear on all report forms to maintain participant confidentiality. During the study, generation and distribution of random number lists, recruitment of subjects, practice by acupuncturists, assessment, data management, and statistical analysis will be independently conducted by different researchers.

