### Blinding

This trial is an open-label trial. It cannot blind the patients and the acupuncturists. Participants are blinded to their group allocation but are informed that they had an equal chance of allocation to the three groups before study participation. The outcome assessor will also be blinded to the group allocation. Adverse reactions are carefully observed, and emergency unblinding is required if serious adverse reactions occur. Unblinding will be performed at the end of the trial to perform statistical analysis.

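### The stated randomisation rule ties contiguous number ranges to arms and describes no mixing; if those numbers set the order of entry or appear on the forms, allocation is predictable or disclosed

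*Protocol article*

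**What the plan says.** The section Randomization and allocation concealment sets out the procedure in steps. A statistician will "generate 3 different random number lists, each of which contains 30 numbers". Then "The random numbers in each list will be sorted in ascending order". The schedule next links number ranges to arms: "no. 1–30 is the acupuncture group, no. 31–60 is TCM-eCBT-I group, and no. 61–90 is the acupuncture combined with TCM-eCBT-I group". After that, "the allocation sequences are enclosed in sealed envelopes with a unique identification number", and the envelopes go to an investigator in charge of assignments, who specifies who opens each one and when. On the forms: "The number will appear on all report forms to maintain participant confidentiality". The section ends with a safeguard: list generation, recruitment, treatment, assessment, data management and analysis "will be independently conducted by different researchers".

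The Blinding section adds "The outcome assessor will also be blinded to the group allocation", and says participants are told that their chance of each of the three groups is equal.

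**The concern.** A valid 1:1:1 sequence needs a step that makes the arm unpredictable from the order of entry. Such a step could be a joint ranking of 90 random numbers, a random permutation, or permuted blocks. The text gives none. It sorts within each of three lists and then assigns consecutive numbers to one arm at a time. Followed literally, this gives 30 acupuncture assignments, then 30 TCM-eCBT-I, then 30 combined.

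Three things are at stake:

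- **Selection bias.** Whoever recruits could foresee the next assignment.
- **Confounding with calendar time.** Each arm would be recruited in its own period.
- **Disclosure.** A schedule number printed on every form would give the arm to anyone who knows the range rule, including the assessor.

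The trial is open-label and its scales are completed by the patients, so unpredictable assignment is one of the few protections against bias left to it. This is not detail left to a fuller document: the article states a rule, and the rule as stated does not randomise the order of entry.

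**Working it through.** **Inputs (protocol article)**

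- Three lists of 30; ranges 1–30, 31–60 and 61–90 (Randomization and allocation concealment).
- 72 cases before loss, 20% loss, 90 in total, 30 per arm (Sample size).
- Recruitment from 20 October 2020, expected to end 31 December 2021 (Trial status).

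**The plan's own total.** 72 / (1 − 0.20) = 90, and 3 × 30 = 90. The schedule therefore covers exactly the planned sample. This checks the count only, not how 72 was obtained.

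**Condition A: schedule numbers are used in order of entry.**

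- Someone who knows the range rule can name 90 of 90 assignments.
- Someone who does not know it, but guesses that each patient gets the same arm as the last, is right for 29 of the 30 patients in each run: 3 × 29 = 87 of 90.
- Calendar time: 20 October 2020 to 20 October 2021 is 365 days, and on to 31 December 2021 is 11 + 30 + 31 = 72 more, so 437 days. With even accrual each arm occupies 437 / 3 ≈ 146 days: roughly days 0–146, 146–291 and 291–437. The recruitment periods of the arms would not overlap.

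**Condition B: the number on the forms is the schedule number.** The range gives the arm for 90 of 90 participants, whatever the order in which envelopes were opened.

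**Comparator: 30/30/30 in random order, with an ID unrelated to arm.**

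- A guesser with no knowledge of past assignments is right for 90 / 3 = 30 of 90 (33%).
- A guesser who knows all past assignments and always names the arm with most places left is right for about 36.8 of 90 (36.8 / 90 = 41%; mean of 5,000 simulated sequences).

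**Does the text establish A or B?** No. For A, it does not say that envelopes are opened in numerical order. For B, the number on the forms most naturally refers back to the envelope's unique identification number, which is never equated with schedule number 1–90. If the two are separate, the form number reveals nothing, and with a mixed sequence guessability is the 33–41% above.

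**The case against.** The best defence is that the passage is badly worded rather than wrong. Suppose the three lists are non-overlapping random draws of 30 from the 90 entry numbers. Sorting each list is then only presentation, the arms are interleaved over entry, and 1–30, 31–60 and 61–90 are positions in the statistician's schedule. This reading gives the random numbers and the sorting a purpose, which they lack on the sequential reading. It also fits better with telling participants that the three groups are equally likely. The method is cited to a reference not shown here, and an article condenses the full protocol.

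This stands as far as it goes. A reader might infer that all 90 IDs reveal the arm however the text is read, or that the trial was not randomised. The document supports neither. It does not support the benign reading either: it never says that the draws come from a common pool of 90, or that the envelope number is separate from the schedule number.

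The stated safeguards must be weighed too. Sealed envelopes and separate staff protect a sequence that cannot be inferred. They do not help if the range rule itself gives the arm away, or if assignments run in blocks of 30 in an open-label single-centre trial.

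The harm through the assessor is limited. Data collection and management has the scales completed online by the subjects themselves, and the Blinding section plans unblinding for the analysis. Selection bias and confounding with time are therefore the larger risks.

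**Conclusion.** The point holds conditionally. What is certain is that the stated rule fixes contiguous ranges to arms, describes no step that mixes the arms over entry, and is followed by a number printed on all forms.

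If numbers were used in order, assignments were predictable (87 to 90 of 90, against 30 to about 37 under a random order), and each arm was recruited in its own period. The figure of about 146 of 437 days is an upper case: it assumes strictly sequential use, even accrual and the recruitment dates under Trial status. If the form number is the schedule number, all 90 forms disclose the arm and the stated assessor blinding fails.

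Neither condition is established. But the rule can be followed to the letter and yield no random order, so it has to be replaced or corrected before the results can be presented as coming from a concealed random allocation.

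**What to change.** **Rule.** Replace the description with a single sequence of 90 in which the arms are randomly permuted over order of entry, for example in permuted blocks of varying size. Very small fixed blocks should be avoided because past assignments are visible in an open-label trial: with a known block size of 3, a guesser is right for 1/3 + 1/2 + 1 = 1.83 of every 3 (61%), against about 41% for one permutation of all 90.

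**Concealment and ID.** Use opaque, sequentially numbered envelopes, opened in order after consent and baseline. Print on the forms only a subject ID that is independent of arm.

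**Which action applies.**

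- If the sequence in use was already mixed and the ID is already independent of arm, correct the text to say so and describe the mixing step. No new list is needed.
- Otherwise, apply the new sequence to the envelopes not yet opened, recode the IDs for assessment and data handling, and report how the opened envelopes were generated and in what order they were used.

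The article is dated 28 January 2022, after the expected end of recruitment, although it describes the trial as recruiting. A new sequence helps only if envelopes remain unopened. Recoding can still help while follow-up is running, and the report on past allocation is useful at any stage.

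**Cost.** A short amendment and relabelling of the remaining envelopes. No extra staff are needed, since list generation and recruitment are already separate.

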### Blinding

This trial is an open-label trial. It cannot blind the patients and the acupuncturists. Participants are blinded to their group allocation but are informed that they had an equal chance of allocation to the three groups before study participation. The outcome assessor will also be blinded to the group allocation. Adverse reactions are carefully observed, and emergency unblinding is required if serious adverse reactions occur. Unblinding will be performed at the end of the trial to perform statistical analysis.

### Participants

#### Inclusion criteria

The inclusion criteria are as follows:
18–60 years old, no gender limitation (either sex)Meeting the diagnostic criteria for chronic insomnia in ICSD-3 [46]PSQI score > 5 points [47]Not accepted in the past month sedative and hypnotic drugs, acupuncture, and CBT-I treatmentHaving smart terminals (such as smartphones, tablets, computers) and knowing how to use WeChatNo communication and cognitive impairment, voluntarily accept random grouping, and sign the informed consent

#### Exclusion criteria

Participants who fulfill any of the following criteria will be excluded:
Complicated with severe physical illnessDiagnosed with depression, schizophrenia, or other serious mental illnessDiagnosed with obstructive sleep apnea, restless leg syndrome, or other sleep disordersIn the past 2 weeks, there are irregular work schedules such as shift work or staying up lateAccompanied by fever, cough, and pain symptoms that seriously affect sleepAlcohol or other drug abuse or dependencePregnancy or lactation which is not suitable to receive acupuncture treatmentInfectious diseases such as infectious hepatitis, tuberculosis, and AIDSParticipated in other clinical studies in the past 3 months

### Interventions

Subjects in the acupuncture group and the acupuncture combined with the TCM-eCBT-I group will all receive the same acupuncture treatment. Acupuncture will be conducted in the outpatient clinic of insomnia. The temperature in the clinic will be kept between 24 and 30°, and the environment is quiet and comfortable. The subjects will be told to relax, close their eyes, and have a rest.

